## Trial governance and safety - adverse events (AE) and serious adverse events (SAE)

6

Both AEs and SAEs will be prospectively recorded for all participants. The drug trial of alternate day iron will only be for a period of 4 weeks and as such, adverse events will only be recorded in this period as following this the participants will revert to routine antenatal care. The investigator will report all serious adverse events immediately to the sponsor except for those that the protocol or investigator's brochure identifies as not requiring immediate reporting. The immediate report will be followed by detailed, written reports. The immediate and follow-up reports will identify subjects by unique code numbers assigned to the latter. The sponsor will report all SUSARs (suspected unexpected serious adverse reaction) to the Health Products Regulatory Authority and the ethics committees concerned.

The trial steering committee will meet quarterly and annual review meeting will be held with UCD Clinical Research Centre with reports provided to the Health Product Regulatory Authority (HPRA) regarding progress, dissemination, and engagement activities in previous 12-month period, and annual development safety update reports will be provided to the NREC by the sponsors. The trial management committee will meet twice a month to review study recruitment and study progress.

Given the established safety of Galfer® in pregnancy to treat iron deficiency anaemia, the fact that it is widely advised in pregnancy, and that the recently updated UK guidelines on the management of iron deficiency anaemia in pregnancy recommend alternate dosing to combat side-effects [40], this trial does not meet the requirement for a Data Safety Monitoring Board as per the EMA's guidance [41]. This is a clinical study of a non-critical indication where the patients are treated for a relatively short time and the drug under investigation is well characterised and known for not harming patients.

## Statistical analysis

7

The primary endpoint, change in haemoglobin from randomisation to week 4, will be analysed by linear regression, adjusting for baseline Hb level and gestation at baseline. Non-inferiority will be evaluated by comparing the lower limit of the 95 % confidence interval for the treatment effect to the non-inferiority margin of −0.4 g/dL. The primary efficacy analysis will be carried out following the intention-to-treat principle, on the Full Analysis Set which is defined as all randomised subjects who received any amount of study drug. A per protocol sensitivity analysis of the primary endpoint will also be conducted on the Per Protocol (PP) set, excluding subjects who were less compliant with their assigned treatment or who switched treatments during the trial.

Intervention effects on numeric secondary endpoints will be estimated using the Full Analysis Set as a between-group difference in means with a 95 % confidence interval, adjusted for gestation at baseline and baseline value (where relevant), using linear regression or generalized linear regression model depending on data distribution. Differences between treatment groups in the patterns of change over time in Hb and ferritin levels will also be explored using linear mixed effects models, with data transformation where necessary. Intervention effects on categorical secondary endpoints will be estimated as a between-group difference in proportions with a 95 % confidence interval, and chi-squared tests will be conducted to compare proportions between groups.

Safety data will be summarized descriptively using the safety set, based on treatment actually received. No interim analysis will be performed for this trial. The statistical analysis plan will be finalized prior to database lock, with any deviations from the original plan documented.

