### Allocation of participants

2.4

Randomisation will take place during the enrolment phase of the trial, after written informed consent is obtained from each trial subject. Each enrolled subject will be assigned a subject identification number that will uniquely identify their record in the study database. Allocation will take place according to a computer-generated variable block randomisation schedule in the ratio 1:1 across the intervention and control arms. Randomisation will be stratified by gestation (14–20 weeks, ≥20+1–28weeks, ≥28+1–34 weeks). The computer-generated randomisation schedule will be stored securely on a password protected computer. The randomisation list will be numbered using sequential 6-digit randomisation codes (e.g. IMA-001, IMA-002) – these are the codes which will uniquely identify each subject. Each arm/group assignment – daily oral iron or alternate daily iron – will be added to an allocation table with its corresponding 6- digit randomisation code. The primary researcher/investigator will obtain the allocation from REDCap (Research Electronic Data Capture), an electronic data capture system which is going to be used for this study [27]. The allocation will be obtained only at the time of randomisation and will not be accessible to the researchers or investigators prior to this point. This is an open-label study. The treatment protocol will not be blinded to investigator, subjects, or medical or nursing staff.

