### Secondary outcomes

5.2

The pre-specified secondary outcomes in IronMother are.i.Compliance as measured by validated questionnaire at the 4-week assessment [38].ii.Tolerance as measured by a validated gastrointestinal symptom questionnaire at the 4-week assessment [39].iii.Compliance as measured by objective pill count at 4-week assessmentiv.Serum ferritin levels in both groups after 4 weeks of treatmentv.Obstetric and neonatal outcomes:•Delivery outcomes (livebirth, stillbirth, neonatal death)•Mode of delivery (vaginal delivery, Caesarean)•Rates and quantitation of primary postpartum haemorrhage•Requirement of a blood transfusion in the two weeks post-delivery•Requirement of a postnatal iron infusion in the two weeks post-delivery•The requirement for any antenatal iron transfusion prior to delivery•Neonatal Outcomes (neonatal high dependency unit or intensive care unit admission, neonatal Apgar scores, Birth weight)•Most recent haemoglobin levels prior to delivery

Exploratory endpoints include measurements such as dietary assessment at trial entry (Food Frequency questionnaire- FFQ), a record of any concomitant medication and/or nutritional supplements and mental wellbeing (WHO-5 wellbeing score) assessment will be also performed at recruitment and the follow-up visit. Blood samples will be taken and stored at baseline and at the follow-up visit 4 weeks' later for processing for other biomarkers of iron metabolism.

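### Categorical secondary endpoints are compared without the gestation strata that the plan adjusts for elsewhere, which costs a little precision but causes no bias

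*Protocol article*

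**What the plan says.** Section 2.4 of the protocol article (Allocation of participants) states: "Randomisation will be stratified by gestation". There are three bands covering 14 to 34 weeks, and within them a "computer-generated variable block randomisation schedule in the ratio 1:1 across the intervention and control arms".

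Section 7 (Statistical analysis) treats the three classes of endpoint as follows.

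- Primary endpoint: it "will be analysed by linear regression, adjusting for baseline Hb level and gestation at baseline".
- Numeric secondary endpoints: a difference in means, "adjusted for gestation at baseline and baseline value (where relevant").
- Categorical secondary endpoints: the estimate is a crude risk difference with its 95% interval. For the test, the article says that "chi-squared tests will be conducted to compare proportions between groups".

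The third entry mentions neither gestation nor any stratified test. The type of confidence interval is not named. Section 5.2 lists the outcomes to which this rule applies. They include mode of delivery, antenatal iron infusion (the article calls it a transfusion), "Requirement of a blood transfusion in the two weeks post-delivery" and "Delivery outcomes (livebirth, stillbirth, neonatal death"). The article gives no event rate for any of them. Section 7 adds that the statistical analysis plan will be completed before the database is locked.

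**The concern.** The factor used to balance the arms is carried into the analysis of two endpoint classes and left out of the third, without a reason. A Pearson chi-squared test takes no covariate, so the method is stated and the article is not merely silent on it.

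The omission matters only where gestation at entry predicts the outcome. The clearest case is antenatal iron infusion: a woman who enters at 14 weeks has many more weeks before delivery in which it can occur than one who enters at 34 weeks. For mode of delivery, postpartum haemorrhage, transfusion or neonatal unit admission, the article offers nothing to show that entry gestation is prognostic.

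Where it is prognostic, stratified allocation has already removed the between-stratum variation from the comparison of arms, but the unstratified standard error still counts it. The interval is then wider than it need be, and the test rejects less often than its nominal level. What is at stake is some precision on secondary endpoints and the consistency of section 7.

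**Working it through.** **The plan's own figure.** Section 3 gives a margin of 0.4 g/dL, SD 0.83, one-sided alpha 0.025, power 90% and 92 per arm. The normal approximation is n = 2(1.96 + 1.2816)² × 0.83² / 0.4² = 90.5, so 91. The noncentral-t version gives 92 (power 90.2%). With 20% dropout, 184 / 0.8 = 230, or 115 per arm. The figures reproduce, but they concern the primary endpoint only. No power or event rate is given for a categorical endpoint, so the stratum risks below are assumptions.

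**Effect on the interval.** Take three equal strata, 1:1 allocation within each, and the same risk p_k in both arms. The unstratified variance is proportional to p̄(1 − p̄), and the stratified variance to the mean of p_k(1 − p_k). The square root of their ratio gives the ratio of interval widths.

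| Assumed risks | p̄(1 − p̄) | Mean of p_k(1 − p_k) | Ratio | Narrower by |
|---|---|---|---|---|
| 20/15/10% | 0.15 × 0.85 = 0.1275 | (0.16 + 0.1275 + 0.09)/3 = 0.1258 | 0.987 | 1 − √0.987 ≈ 0.7% |
| 30/15/5% | 0.1667 × 0.8333 = 0.1389 | (0.21 + 0.1275 + 0.0475)/3 = 0.1283 | 0.924 | 1 − √0.924 ≈ 4% |
| equal in all strata | – | same as p̄(1 − p̄) | 1 | 0 |

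**Effect on the test.** This was simulated with 200,000 replicates, 92 per arm and near-equal strata balanced within stratum, at the two-sided 5% level. Power is for a 20-point increase in every stratum of one arm. CMH is the Cochran-Mantel-Haenszel test.

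| Assumed risks | Null rejection, chi-squared | Null rejection, CMH | Power, chi-squared | Power, CMH |
|---|---|---|---|---|
| 30/30/30% | 5.0% | 4.9% | 79.3% | 79.3% |
| 20/30/40% | 4.7% | 4.9% | 79.8% | 81.1% |
| 10/30/50% | 3.7% | 5.0% | 81.0% | 84.4% |
| 5/30/70% | 1.9% | 5.0% | 81.3% | 91.0% |

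The chi-squared test is never anti-conservative here. The loss is negligible for flat or mild gradients and becomes large only for very steep ones.

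**Very rare outcomes.** An expected count of five events per arm needs a rate of at least 5/115 = 4.3% (5/92 = 5.4% with 92 per arm). With 230 women the chance of no event at all is (1 − p)^230, which is 63%, 40% or 32% for assumed rates of 0.2%, 0.4% or 0.5%. The chi-squared statistic is then undefined. With a few events the choice of test can matter: 0 versus 4 events at 92 per arm gives p = 0.043 by chi-squared and p = 0.121 by Fisher's exact test. Even so, the exact type I error of the uncorrected chi-squared test stayed at or below about 5.2% at every rate tried, from 0.3% to 30%.

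**The case against.** The best defence is that very little is lost. With 1:1 blocks within strata the crude risk difference is unbiased, and ignoring the strata errs on the cautious side. The gain is under 1% of interval width for a mild gradient and about 4% for a six-fold one. The prognostic argument is plausible for antenatal iron infusion and unsupported by the article for the other outcomes. All of this stands, and it sets the severity.

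A reader might go further and infer that the planned method fails for stillbirth, neonatal death and transfusion because it would give an interval of zero width. The article does not support that. It names no interval type; zero width with no events is a property of the Wald interval, and score-type intervals also fit the wording. It gives no event rates, so the chances of no event above are illustrations, and nothing ties those rates to transfusion. A rule for small expected counts is commonly left to the statistical analysis plan, which is not shown. Fisher's test would not rescue an empty table either, since it returns p = 1.

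It can also be said that an unstratified interval for the rarest outcomes abandons the strata again. That is true, but with a handful of events there is little between-stratum variation to remove.

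**Conclusion.** The inconsistency within section 7 is real: gestation is adjusted for in the primary and numeric secondary analyses, and no adjustment is stated for the categorical ones. The consequence is a standard error that is too large, and a conservative test, for those outcomes on which gestation at entry has an effect. Under the assumed gradients the interval would be about 0.7% to 4% narrower with stratification, with little or no gain if risk does not vary by gestation. These figures rest on assumed stratum risks, equal strata and balance within strata.

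It would be wrong to conclude that the treatment comparison is biased or that false positives are inflated; neither follows from the design, and the calculations show neither. The sample size and the non-inferiority conclusion are unaffected. This is a low-severity improvement in efficiency and consistency.

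**What to change.** For categorical secondary endpoints, replace the crude comparison with a gestation-stratified risk difference (Mantel-Haenszel, or stratified Miettinen-Nurminen) with a 95% confidence interval, and replace the chi-squared test with the Cochran-Mantel-Haenszel test over the three randomisation strata.

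As a minor addition, which the statistical analysis plan may already contain: for very rare outcomes such as stillbirth and neonatal death, report the counts by arm with a score or exact interval, and do not rely on a chi-squared p-value. Fixing this in advance avoids choosing the method after the counts are known.

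The cost is a sentence or two in the statistical analysis plan and a few lines of code. The strata are already recorded for randomisation, and section 7 leaves the analysis plan open until database lock.

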## Discussion

8

The purpose of this randomised controlled trial is to determine if alternate day ferrous fumarate is as effective as daily ferrous fumarate for the treatment of confirmed iron deficiency anaemia in pregnancy. In light of recent compelling scientific evidence of the advantages of alternate day oral iron, it is timely to examine the benefit in pregnancy. This study is novel in assessment of both dosing regimens in an Irish pregnancy population with confirmed iron deficiency anaemia. We hypothesise that alternate day iron will be as effective as daily iron but with a better side-effect profile.
